## Materials and methods

Study design and setting

This study will be conducted as a parallel-designed, prospective, assessor-blinded, single-center randomized controlled trial. The timeline of this protocol study is from August 2024 to May 2025. This study will take place at the Department of Tui Na and the Psychosomatic Medicine Outpatient Department of the First Teaching Hospital of Tianjin University of Traditional Chinese Medicine, China. Seventy GAD patients will be randomly allocated to either the combined abdominal massage and medication group or the medication-only group. The study will involve various scale assessments, EEG examinations, and stool sample collections both pre- and post-intervention. Additionally, 35 healthy participants will be recruited to serve as normal controls and will undergo relevant tests and examinations upon enrollment. The trial flowchart is depicted in Figure 1, and the study timeline is outlined in Figure 2.

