Participants will be excluded if they have anxiety states induced by physical conditions such as hypertension, Sjögren's syndrome, hyperthyroidism, or coronary heart disease. Additionally, individuals currently taking medications that may cause anxiety or those experiencing withdrawal symptoms from long-term use of anti-anxiety medications will be excluded. Anxiety states linked to other mental disorders will also be grounds for exclusion. Patients with severe liver or kidney dysfunction who cannot adhere to the medication regimen, as well as those known to be allergic to any components used in this study, will not be eligible. Furthermore, pregnant or breastfeeding women will be excluded from participation.

Inclusion Criteria for Healthy Participants

Participants must be between 18 and 65 years old, regardless of gender, and should be right-handed. They must be in good health, without any physical discomfort in the past month. Individuals who have undergone central nervous system stimulation, such as repetitive transcranial magnetic stimulation (rTMS), transcranial direct current stimulation (tDCS), or peripheral nervous system stimulation, such as acupuncture or electroacupuncture, will be excluded. Additionally, candidates must have no history of illegal drug use or alcohol abuse. All participants must voluntarily sign the informed consent form and agree to take part in the survey.

Randomization and Assessor-Blinding

Patients with GAD will be randomly assigned to either the treatment group or the control group using computer-generated random numbers. The random sequences, identified with unique labels, will be sealed in opaque envelopes, which will only be opened upon the enrollment of a participant. The sequence generation and allocation will be carried out by independent personnel who are not involved in the trial. Healthy participants will be enrolled as normal controls, without undergoing randomization.

Blinded assessments will be performed, with patients receiving treatment in distinct settings. Efficacy will be evaluated by a third party who is not privy to the group assignments. During data aggregation, blinded statistical analysis will be conducted. Throughout the study, researchers, clinical operators, efficacy evaluators, and data statisticians will maintain separation to ensure the integrity of the blinding process.

Sample Size

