**Figure 3 FIG3:**
[figure not shown]
Acupoint location diagram.

Control Group GAD Patients

Medication includes oral escitalopram (Bailex) (Sichuan Kelun Pharmaceutical Co., Ltd., China; approval no.: National Drug Standard H20080788; specification: 10 mg × 10 tablets), 10 mg once daily at 09:00 AM for eight weeks.

Healthy Participants

Healthy participants will not receive any treatment. They will be screened based on their medical history and HAMA scores. General information and HAMA scores will be recorded. Upon enrollment, EEG and stool samples will be collected from healthy participants.

Statistical analysis

This study will conduct statistical analysis based on the principle of intention-to-treat (ITT), including all patients who entered randomization and were not excluded in the statistical analysis. The efficacy endpoints will be analyzed using the full analysis set (FAS), supplemented by the per-protocol set (PP). Safety endpoints will be analyzed using the safety set (SS).

IBM SPSS Statistics for Windows, Version 26 (Released 2019; IBM Corp., Armonk, New York, United States) will be used for statistical processing. Measurement data will first be tested for normal distribution and homogeneity of variance. Data that meet the normal distribution and homogeneity of variance will be statistically described using the mean ± standard deviation (x̄±s), and data that do not meet the normal distribution and homogeneity of variance will be statistically described using the median (M) and the 25th and 75th percentiles (P_25_, P_75_).

For the comparison of measurement data between two groups, a paired two-sample t-test will be used for data that meet the normal distribution, and a rank-sum test will be used for data that do not meet the normal distribution. For the comparison of data at different time points after treatment with pre-treatment data, a paired t-test will be used for data that meet the normal distribution, and a rank-sum test will be used for data that do not meet the normal distribution. For the comparison of measurement data among multiple groups, a one-way ANOVA will be used for data that meet the normal distribution, and a rank-sum test will be used for data that do not meet the normal distribution.

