For the comprehensive comparison of measurement data at different time points between two groups, a repeated measures ANOVA will be used if the data meet the sphericity assumption and a Friedman test will be used if the data do not meet the normal distribution. Count data will be statistically described using case number and composition ratio, and the comparison between groups will be performed using the χ² test. Rank data will be analyzed using the two-sample non-parametric rank-sum test. The significance level for all tests will be α=0.05.

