## Results

Primary outcome

The primary outcomes of this study will be determined by the HAMA [18] scores and electroencephalogram (EEG) results. The HAMA scale consists of 14 items, which will be evaluated by professional psychiatrists before and after the treatment. The total HAMA score can range from 0 to 56, with anxiety levels classified as follows: possible anxiety for scores between 7 and 14, definite anxiety for scores between 14 and 21, moderate anxiety for scores between 21 and 29, and severe anxiety for scores greater than 29.

For the EEG, participants will be seated in a quiet environment, with their eyes closed, while maintaining an alert state. Scalp electrodes will be placed according to the international 10-20 system, using 17 disc electrodes with earlobes serving as reference electrodes. The EEG will record both bipolar and reference leads, with standard evoked tests (including hyperventilation, rhythmic photic stimulation, and eye-opening/closing tests) conducted during monitoring. The time constant will be set at 0.3 ms, the high-frequency filter will be set at 70 Hz, the standard voltage will be set at 10 mV/mm, and the recording time will be between 15 and 20 minutes.

Other outcome measures

Other outcome measures in this study include symptom signs, scores on the Hamilton Depression Rating Scale (HAMD), scores on the Symptom Checklist-90 (SCL-90), and results from monitoring the gut microbiota.

Hamilton Depression Rating Scale

This scale is used to assess the severity of depression in patients and consists of 17 items. Depression severity is classified based on HAMD scores as follows: a score of less than 7 suggests no depression; a score between 7 and 16 suggests possible depression; a score of 17 or greater indicates definite depression.

Symptom Checklist-90

This scale is used to evaluate patients' self-perceived symptoms during treatment. Each question is rated on a scale from 1 (none) to 5 (severe), with higher scores indicating more severe adverse symptoms.

Gut Microbiota Monitoring

Stool samples will be collected from randomly selected patients in the treatment and control groups before and after eight weeks of treatment. Samples will be collected in the morning, on an empty stomach, using a sterile spoon to obtain 3-5 g of fresh stool. These samples will be immediately placed in standardized sterile containers and stored at -80°C for subsequent analysis [19].

Safety assessments

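### The between-group comparison of measurement data is assigned a paired t-test, although the randomised arms are independent and the sample size assumes an independent test

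*Protocol article*

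**What the plan says.** The Statistical analysis section of the protocol article gives a rule for each kind of comparison.

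- Between two groups: "For the comparison of measurement data between two groups, a paired two-sample t-test will be used for data that meet the normal distribution". Otherwise, "a rank-sum test will be used for data that do not meet the normal distribution".
- After treatment against before, in the next sentence: "For the comparison of data at different time points after treatment with pre-treatment data, a paired t-test will be used" when the data are normal. The non-normal fallback is again called a rank-sum test.
- Two groups over several time points: "For the comprehensive comparison of measurement data at different time points between two groups, a repeated measures ANOVA will be used", on condition that sphericity holds.

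On the design, Study design and setting states: "This study will be conducted as a parallel-designed, prospective, assessor-blinded, single-center randomized controlled trial". Randomization and Assessor-Blinding adds: "Patients with GAD will be randomly assigned to either the treatment group or the control group using computer-generated random numbers". Neither section mentions matching, crossover or any other source of pairs.

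On outcomes, the Primary outcome section states: "The primary outcomes of this study will be determined by the HAMA [18] scores and electroencephalogram (EEG) results". HAMA is a numerical score, so it is measurement data and the two-group rule covers it.

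The Sample Size section gives a medication-group HAMA of 18.61 with SD 3.17, an anticipated decrease of 2.76 points, two-sided alpha 0.05 and 90% power. It arrives at N1 = 29 and N2 = 29, raised to 35 per group for dropout.

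**The concern.** A paired t-test works on differences within pairs that exist by design: the same patient twice, or deliberately matched patients. Here each patient is randomised alone to one arm. To run the stated test, someone would have to set each massage patient beside some medication-only patient, and nothing in the article says how.

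Two things are at stake. First, the result would not be a function of the data alone: the mean difference is the same under every line-up, but its standard error changes with the line-up. Row order in the data file could then decide a borderline result. Second, a paired test needs equal numbers. If the arms finish with different numbers of evaluable patients, the surplus in the larger arm cannot be used, which sits badly with the section's own intention-to-treat and full-analysis-set commitment.

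The wording cannot be read as a loosely phrased within-patient test, because the next sentence covers that comparison separately.

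**Working it through.** **Inputs** (Sample Size section): difference d = 2.76, read as the between-arm difference; common SD s = 3.17; two-sided alpha 0.05; target power 90%; stated n = 29 per arm; 20% dropout; 35 per group enrolled.

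**Step 1: reproduce the stated 29 per arm with an independent t-test.** Degrees of freedom are 2n − 2, the noncentrality is d / (s·√(2/n)), and power comes from the noncentral t distribution.

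| n per arm | df | noncentrality | critical t | power |
|---|---|---|---|---|
| 28 | 54 | 2.76 / (3.17·√(2/28)) = 3.258 | 2.005 | 0.892 |
| 29 | 56 | 2.76 / (3.17·√(2/29)) = 3.315 | 2.003 | 0.903 |

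The smallest n that reaches 90% is 29, exactly the stated figure.

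**Step 2: try the paired test.** Degrees of freedom are n − 1, and the noncentrality is d·√n / SD of the differences.

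- Unrelated patients (correlation zero): the SD of the differences is 3.17·√2 = 4.483. Power is 0.892 at 29 pairs and 0.903 at 30 pairs, so 30 pairs are needed.
- If 3.17 were itself the SD of the differences: power is 0.880 at 15 pairs and 0.902 at 16, so 16 pairs are needed.

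Neither variant gives 29. The sample size rests on the independent test.

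**Step 3: cost in power at equal n.** With unrelated patients the noncentrality is the same for both tests. The paired test loses only degrees of freedom, and so has a larger critical value.

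| n per arm | independent | paired, arbitrary line-up | loss |
|---|---|---|---|
| 29 | 0.903 | 0.892 (critical t 2.048) | about 0.01 |
| 28 (= 35 × 0.8) | 0.892 | 0.881 (critical t 2.052) | about 0.01 |

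**Step 4: type I error.** In 100,000 simulated trials with 29 per arm and no true difference, the paired test on arbitrary line-ups rejected in 0.0495 and the independent test in 0.0491. There is no inflation.

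**Step 5: dependence on the line-up.** One data set was simulated with 29 per arm, SD scaled to 3.17 and the mean difference set at 1.8, so that the independent test gives p = 0.035. The arms were then re-paired at random 20,000 times. The paired p-value ran from 0.011 to 0.075 (central 95%, median 0.039), and 73% of line-ups gave p < 0.05. This is a single illustration, chosen near the significance boundary. It shows the mechanism, not how often a conclusion would flip.

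**The case against.** The strongest reply is that this is a slip of one word. Homogeneity of variance is to be checked first, which matters for an independent t-test and not for a paired one. The fallback is a rank-sum test, the independent-samples method. The sample size gives separate N1 and N2. All of this suggests that an independent test was meant, and it lowers the chance that the wrong test would be run. It does not remove the error: the article positively names a test that its design cannot support. This is not detail left to a fuller document.

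Three stronger readings are tempting but not supported.

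- **A reader might infer that this is the main efficacy test, or the test named for HAMA.** No test is named for HAMA or labelled primary. The repeated measures ANOVA for two groups over time could equally serve a score taken before and after treatment, and it needs no pairing across arms.
- **A reader might infer a large power loss from dropout.** If pairs were fixed at enrolment and lost whenever either member left, about 0.8 × 0.8 × 35 = 22 would remain, with power near 0.79. The article forms no such pairs. The 28 completers per arm could be lined up afterwards, with power 0.881. Setting 22 pairs against 29 per arm mostly compares sample sizes: an independent test with 22 per arm has power 0.805.
- **A reader might infer that a wrong non-parametric test is planned for pre/post data.** The pre/post sentence reads "a paired t-test will be used for data that meet the normal distribution, and a rank-sum test will be used". The article also uses the term rank-sum for two groups and for several groups, so it may be an umbrella label. This deserves a wording correction and no more.

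Nothing in the article shows unequal variances, so insisting on the Welch form would be a preference.

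**Conclusion.** The stated two-group rule is wrong for this design and inconsistent with the article's own sample size. It should be corrected because it governs between-arm comparisons of measurement data, HAMA among them. The case rests on correctness, not on a large numerical effect: the p-value would depend on an arbitrary ordering, and surplus patients would be lost when arm sizes differ. Type I error is not inflated, about one percentage point of power is lost at equal n, and the 29 evaluable patients per arm stand unchanged once the test is corrected.

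These figures assume normal data with common SD 3.17, a true between-arm difference of 2.76 and no correlation between patients lined up across arms.

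**What to change.** In Statistical analysis, replace the paired two-sample t-test in the two-group sentence with an independent two-sample t-test, and name the Mann-Whitney (rank-sum) test as its non-normal fallback. Keep the paired t-test for within-patient change from before to after treatment only.

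As a minor wording correction in the same edit, name the Wilcoxon signed-rank test as the non-normal fallback for the pre/post comparison.

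The cost is a few words in one section. The number of evaluable patients, the procedures and the data collected do not change. The edit should be made before outcome data by arm are seen, so that the choice between the two tests cannot be influenced by the results.

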Based on prior research, the Hamilton Anxiety Rating Scale (HAMA) score for the medication group was 18.61±3.17 [14]. The HAMA score for the treatment group is anticipated to decrease by 2.76 points. With a two-sided significance level (α) of 0.05 and a power of 90%, the required sample size was calculated using PASS 2021 software. This resulted in a needed sample size of N1=29 for the treatment group and N2=29 for the control group. Taking into account a potential dropout rate of 20%, a minimum of 35 subjects per group is needed, amounting to a total of at least 70 subjects. In addition, 35 healthy participants will be included in the study.

Intervention

Treatment Group GAD Patients

The medication regimen for this study will consist of oral escitalopram (Bailex) (Sichuan Kelun Pharmaceutical Co., Ltd., China; approval no.: National Drug Standard H20080788; specification: 10 mg × 10 tablets) [15]. Each participant will take 10 mg once daily at 09:00 AM for a duration of eight weeks.

In addition to the medication, participants in the treatment group will receive abdominal massages. The massage procedure will follow guidelines from the "Tui Na" textbook [16] edited by Fang Min and Wang Jingui (5th edition, "14th Five-Year Plan" for higher education in TCM). Participants will lie in a supine position while the practitioner performs rhythmic circular motions on the abdomen with the palm, 5 minutes clockwise and 5 minutes counterclockwise, at a frequency of 120 times/min. This is followed by finger massage on Zhongwan, Tianshu, Qihai, and Guanyuan points for 5 minutes at a frequency of 160 times/min. The total treatment time is approximately 15 minutes, conducted once daily, five days a week, for eight weeks.

To ensure the quality of the abdominal massage and the precise location of the acupoints, several measures will be implemented. Prior to the trial, [name] massage techniques, including force and frequency, will be calibrated using the YF-3 Hand Technique Measurement Instrument to create a standardized model. During the trial, experienced physicians with over 10 years of clinical practice will carry out the procedures. Additionally, all operators will receive training to ensure their techniques align with the model established by the YF-3 instrument.

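### The stated t-test for between-group comparisons of measurement data is a paired one, although the two arms are independent, individually randomised patients with no matching

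*Protocol article*

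**What the plan says.** All places are in the protocol article.

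- **Statistical analysis, between groups:** "For the comparison of measurement data between two groups, a paired two-sample t-test will be used for data that meet the normal distribution", with a rank-sum test if the data are not normal.
- **Statistical analysis, within patients (the next sentence):** "For the comparison of data at different time points after treatment with pre-treatment data, a paired t-test will be used", again with a rank-sum fallback.
- **Statistical analysis, over time between groups:** "For the comprehensive comparison of measurement data at different time points between two groups, a repeated measures ANOVA will be used", subject to sphericity.
- **Study design and setting:** "This study will be conducted as a parallel-designed, prospective, assessor-blinded, single-center randomized controlled trial".
- **Randomization and Assessor-Blinding:** "Patients with GAD will be randomly assigned to either the treatment group or the control group using computer-generated random numbers". No matching or pairing of patients is mentioned there or elsewhere.
- **Sample Size:** "the Hamilton Anxiety Rating Scale (HAMA) score for the medication group was 18.61±3.17". With an anticipated 2.76-point reduction, two-sided alpha 0.05 and 90% power, this leads to a "needed sample size of N1=29 for the treatment group and N2=29 for the control group". An allowance for 20% dropout raises it to 35 per group.
- **Primary outcome:** "The primary outcomes of this study will be determined by the HAMA [18] scores and electroencephalogram (EEG) results". No sentence says which of the listed tests decides the HAMA comparison.

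The same section commits to intention-to-treat, with efficacy analysed in the full analysis set.

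**The concern.** A paired t-test needs a real link between each observation in one column and one observation in the other. Pre- and post-treatment scores of the same patient have such a link. Two arms of individually randomised patients do not. Because the pre/post case has its own sentence, the first sentence cannot be read as a loose description of the within-patient test.

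If an analyst follows the text, row i of one arm is set against row i of the other. Three things follow:

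- The result is not a unique function of the data. Re-sorting the file changes the standard error and the p-value, while the mean difference stays the same.
- With unequal numbers of evaluable patients, those without a partner drop out of the test, which conflicts with the full analysis set.
- The degrees of freedom halve, from 2n − 2 to n − 1.

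HAMA is a measurement variable and a primary outcome, so a simple two-arm comparison of HAMA comes under this rule.

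**Working it through.** **Inputs.** From Sample Size: difference 2.76 points (read as a between-group difference), SD 3.17, two-sided alpha 0.05, power 90%, 29 evaluable per group, 35 recruited per group, 20% dropout. Completer splits, observed differences and simulated scores below are assumptions and are labelled as such.

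**1. Reproduce the plan's figure with an independent-samples t-test.**
SE = SD × √(2/n); noncentrality = 2.76/SE; df = 2n − 2.
- n = 28: SE = 3.17 × √(2/28) = 0.847; noncentrality 3.258; df 54; power 0.892.
- n = 29: SE = 3.17 × √(2/29) = 0.832; noncentrality 3.315; df 56; power 0.903.

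The smallest n reaching 90% is 29, which is the stated N1 = N2.

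**2. The same target with a paired t-test on unrelated rows.**
SD of differences = 3.17 × √2 = 4.483; SE = 4.483/√n; df = n − 1.
- 29 pairs: noncentrality 3.315, df 28, power 0.892.
- 30 pairs: noncentrality 3.372, df 29, power 0.903.

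So 30 pairs are needed at zero correlation. If 3.17 is instead taken as the SD of the differences, 16 pairs suffice. At a small assumed between-row correlation of about 0.04, the paired test also reaches 90% at 29 pairs (power 0.904).

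**3. Unequal completers (assumed 24 versus 32).**
- Independent: SE = 3.17 × √(1/24 + 1/32) = 0.856; noncentrality 3.224; df 54; power 0.886.
- Paired: 24 pairs only, 8 patients dropped; SE = 4.483/√24 = 0.915; noncentrality 3.016; df 23; power 0.823.

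**4. Dependence on row order (assumed data).** 35 × 0.80 = 28 per arm. Scores were simulated with each arm's SD set to exactly 3.17. One arm was then shuffled 4,000 times and the paired test repeated.

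| Observed difference | Independent t (df 54) and p | Paired p, central 95% of row orders | Share of orders with p < 0.05 |
|---|---|---|---|
| 1.9 | 1.9/0.847 = 2.24; p = 0.029 | about 0.009 to 0.066 | about 84% |
| 1.7 | 1.7/0.847 = 2.01; p = 0.050 | about 0.017 to 0.099 | about 42% |
| 2.76 | 2.76/0.847 = 3.26; p = 0.002 | about 0.0003 to 0.010 | 100% |

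The last digits and shares shift slightly with the simulated data set.

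**5. Type I error (simulation, 29 per arm, no true difference).** With row order unrelated to outcome, the paired test rejects in about 4.9% of trials, against 4.8% for the independent test. If both columns are sorted by outcome before pairing, it rejects in about 66%.

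**The case against.** **A wording slip.** The phrase contradicts itself, and the separate N1 and N2 fit an independent test, so the authors may have meant that. This is probably right. It does not remove the point, because the published sentence is the pre-specified rule and it names an invalid test. The rank-sum fallback is weak evidence either way, since the section uses the same term for pre/post and multi-group data.

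**Is this the primary HAMA test?** A reader might infer that the paired test is the stated test for the main efficacy comparison. The article does not say so. HAMA is measured before and after treatment in two arms, so the repeated measures ANOVA in the same section fits at least as well. The paired test is one of two candidates. The ANOVA does not repair the faulty sentence, which still governs every simple two-group comparison.

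**Healthy controls.** A reader might also infer that 70 patients would be paired with 35 healthy participants, discarding half the patients. The article gives one-way ANOVA for more than two groups and does not say that the patients will be pooled for a two-group t-test, so this is not supported.

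**Size.** The 1.9- and 1.7-point examples lie close to p = 0.05 by choice. At the planned difference no order tried lost significance, and the power loss with equal arms is about one percentage point. The 24 versus 32 split is not in the document. The 66% error rate requires sorting both arms by outcome, which nothing in the article suggests. All of this stands and limits the practical harm.

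**Sample size as evidence.** It would be too strong to say that 29 arises only from an independent test, since a small positive correlation also gives 29 pairs. The independent reading is simply much the more natural one.

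**Conclusion.** The point holds. The rule for comparing normally distributed measurement data between two groups names a test that the parallel, unmatched design cannot support.

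The main harm is a p-value that depends on file order, together with the loss of unpaired patients despite the full analysis set commitment. The cost in power is small if the arms are equal and row order is arbitrary (90.3% to 89.2% at 29 per arm). It grows with imbalance (88.6% to 82.3% at an assumed 24 versus 32). Row order can change the conclusion for results near the significance boundary, but did not do so at the planned 2.76 points.

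These figures assume normal scores, a common SD of 3.17 and no correlation between rows. HAMA is affected by the general rule for measurement data; no explicit statement makes this its primary test.

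**What to change.** In the Statistical analysis section, replace the paired two-sample t-test for between-group comparisons with an independent-samples t-test, reporting the mean difference with its 95% CI. Either the equal-variance or the Welch form will do: the section already plans a check of variance homogeneity, and the equal-variance form is the one that reproduces 29 per group. Keep the paired t-test for within-patient pre/post comparisons only.

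The cost is one sentence of wording. No new data are needed, and the sample size stays at 29 evaluable per group.

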## Abstract

Introduction and aim: Generalized anxiety disorder (GAD) is a prevalent mental health condition characterized by excessive, often uncontrollable anxiety, frequently accompanied by autonomic dysfunction symptoms. The gut-microbiota-brain axis is implicated in its pathogenesis. Traditional Chinese medicine therapies, including abdominal massage, are increasingly being considered for GAD treatment. This study is designed to evaluate the therapeutic potential of abdominal massage for GAD and its influence on patients' gut microbiota.

Materials and methods: A prospective, assessor-blinded, single-center randomized controlled trial involving 70 GAD patients, randomly allocated to either a combined abdominal massage and medication group or a medication-only group will be conducted. An additional 35 healthy individuals will serve as normal controls.

Results: The primary outcome measure will be the Hamilton Anxiety Rating Scale (HAMA) score pre- and post-treatment. Participants will undergo electroencephalogram (EEG) assessments and provide stool samples for gut microbiota evaluation. Differences between GAD patients and healthy controls will be compared, and changes in the two GAD groups pre- and post-treatment will be monitored. Subsequently, the correlation between EEG findings, gut microbiota, and clinical efficacy in GAD patients will be analyzed.

Conclusion: This study seeks to confirm the therapeutic benefits of abdominal massage for GAD and offer preliminary insights into its underlying mechanisms. Changes in these indicators before and after treatment in both the treatment and control groups will be examined to clarify the potential mechanisms by which abdominal massage may benefit GAD patients. Abdominal massage is hypothesized to alleviate clinical symptoms in GAD patients by modulating the gut-brain axis. If our hypothesis is validated, abdominal massage could emerge as a new alternative treatment for GAD and offer fresh insights into the mechanisms underlying massage therapy. The study's findings will be disseminated through peer-reviewed publications.

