## Conclusions

This is the first randomized controlled trial to incorporate abdominal massage into the gut-brain axis framework for GAD patients. EEG and gut microbiota are indicators of gut-brain axis function. Differences in these indicators between GAD patients and healthy individuals will be identified to determine the characteristics of gut-brain interactions in GAD patients. Furthermore, changes in these indicators before and after treatment in the treatment group and the control group will be studied to elucidate the potential mechanisms of abdominal massage in treating GAD patients. The main advantage of this study is the collection and evaluation of multifaceted data. Abdominal massage is hypothesized to improve clinical symptoms in GAD patients by regulating the gut-brain axis. If this hypothesis is confirmed, abdominal massage will not only become a new alternative method for treating GAD but also provide new insights into the mechanisms of massage therapy.

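### The omnibus three-group ANOVA does not isolate the GAD-versus-healthy contrast; one planned contrast of pooled baseline GAD patients against healthy participants would, with moderately more power

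*Protocol article*

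**What the plan says.** The Statistical analysis section of the protocol article sets tests by the number of groups.

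- More than two groups: "For the comparison of measurement data among multiple groups, a one-way ANOVA will be used for data that meet the normal distribution". If the data are not normal, an unspecified rank-sum test replaces it. The sentence names no groups, outcome, time point or contrast.
- Two groups: "For the comparison of measurement data between two groups, a paired two-sample t-test will be used for data that meet the normal distribution", again with a rank-sum test otherwise. The rule is not limited to the randomised arms.
- Ordinal data, as a separate item: "Rank data will be analyzed using the two-sample non-parametric rank-sum test".

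The question about healthy participants is put as a two-sided comparison. The Abstract says "Differences between GAD patients and healthy controls will be compared, and changes in the two GAD groups pre- and post-treatment will be monitored". The Conclusions say "Differences in these indicators between GAD patients and healthy individuals will be identified to determine the characteristics of gut-brain interactions in GAD patients", and take up change under treatment as a further, separate question.

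On the data available, the Healthy Participants section says "Upon enrollment, EEG and stool samples will be collected from healthy participants", and no later visit is described for them. On numbers, the Sample Size section gives 35 patients per randomised arm and adds "In addition, 35 healthy participants will be included in the study".

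**The concern.** The only set of more than two groups in this trial is massage plus escitalopram, escitalopram alone, and healthy. The ANOVA rule can therefore apply only to comparisons that include the healthy participants, yet the hypothesis it tests is not the one the article asks about.

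Before treatment, the two GAD arms differ only by chance. A three-group F test asks whether any of three means differ, and so uses one of its two degrees of freedom on a difference that randomisation makes null. Two things follow. A significant F does not establish that GAD differs from healthy. And when GAD does differ, the test is less likely to detect it than a test aimed at that contrast using all 70 patients together.

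At stake is the description of gut-brain characteristics in GAD, which the Conclusions rest on this comparison. EEG is directly affected: the Primary outcome section lists it as a primary outcome, and the healthy participants provide it.

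**Working it through.** **The plan's own figure first.** The only powered comparison is HAMA between the two randomised arms. Inputs from Sample Size: difference 2.76, SD 3.17, two-sided α 0.05, power 90%. The standardised difference is 2.76/3.17 = 0.871. An exact two-sample t-test has power 0.892 at 28 per arm and 0.903 at 29 per arm, so the stated 29 is reproduced. No sample-size or power figure is given for GAD versus healthy.

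**Inputs for the check.** Group sizes 35/35/35 and α = 0.05 are from the article. The GAD-versus-healthy effect d, in SD units, is not in the article, so a range of 0.3 to 0.8 is assumed. Also assumed are a common SD, equal baseline means in the two randomised arms, and a measurement on every participant.

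**Omnibus test.** With means (d, d, 0) the grand mean is 2d/3. The noncentrality is

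λ = 35 × [2 × (d/3)² + (2d/3)²] = 35 × 6d²/9 = 23.33 d².

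Power is taken from the noncentral F with 2 and 102 df; the 5% critical value is 3.085.

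**Direct contrast, 70 pooled GAD versus 35 healthy.** The noncentrality of t is

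δ = d / √(1/70 + 1/35) = d / √(3/70), so δ² = 23.33 d².

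Power is taken from the noncentral t with 102 df; the two-sided 5% critical value is 1.983.

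Both tests carry the same signal, since λ = δ². The contrast concentrates it on one numerator degree of freedom and the omnibus test spreads it over two. At d = 0.6, λ = δ² = 23.33 × 0.36 = 8.4; the omnibus power is 0.726 and the contrast power 0.819.

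| Assumed d (SD) | Omnibus ANOVA | Direct contrast | Loss (points) |
|---|---|---|---|
| 0.3 | 0.229 | 0.300 | 7 |
| 0.4 | 0.381 | 0.482 | 10 |
| 0.5 | 0.558 | 0.667 | 11 |
| 0.6 | 0.726 | 0.819 | 9 |
| 0.7 | 0.856 | 0.918 | 6 |
| 0.8 | 0.936 | 0.969 | 3 |

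The largest loss is about 11 points, near 0.48 SD. The difference detectable with 80% power is 0.65 SD for the omnibus test and 0.59 SD for the contrast.

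**Sensitivity to fewer GAD patients.** With 28/28/35 (20% fewer in each arm) the pattern is the same: 0.687 against 0.786 at 0.6 SD.

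**Limit of the figures.** They apply where everyone is measured, as for EEG. The Gut Microbiota Monitoring section takes stool from randomly selected patients without giving their number, so no power figure can be stated there.

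**Does the two-group rule supply the direct test?** Only in part. For normal data it names a paired t-test, and 70 patients and 35 unrelated healthy participants form no pairs. For non-normal data its rank-sum test would serve if the two arms were pooled, but pooling is nowhere stated.

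**The case against.** The strongest reply is that the article never assigns GAD versus healthy to the ANOVA. The Abstract and Conclusions word the question as two groups, a two-group rule exists, and it is not confined to the randomised arms. On that reading the direct test is already planned. This stands far enough that one cannot say the contrast goes untested. It does not settle the matter, because the rule as worded is for paired data and the arms are not said to be pooled, while the ANOVA rule has no use in this trial other than comparisons with healthy participants.

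A second reply is that a condensed article may leave contrasts and post hoc tests to a fuller plan, and that an omnibus ANOVA is a valid test. Both are fair. The absence of post hoc detail is not the point here; the point is that a stated test does not match the stated question. The gain is one of efficiency and clarity, not the correction of an invalid test.

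Three stronger readings are tempting and are not supported:

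- *That the multi-group rank test is a two-sample test.* The article uses that term for rank data only. The multi-group fallback is imprecisely named, and a multi-sample rank test may be meant.
- *That three pairwise tests with inflated family error are planned.* No such tests are described.
- *That a week-8 comparison would mix disease with escitalopram.* Healthy participants are measured once, at enrolment, and no later comparison with them is stated. The time point of the multi-group test is merely unspecified.

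**Conclusion.** The point holds in a limited form. The method stated for more than two groups does not isolate the GAD-versus-healthy contrast that the article asks about, and the two-group rule does not, as worded, fit independent GAD and healthy participants.

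If the omnibus test is the one used at baseline, the cost is moderate: 3 to 11 power points over assumed effects of 0.3 to 0.8 SD. This rests on the assumed effect sizes, equal baseline means in the two arms, a common SD and complete measurement. The randomised HAMA comparison and its sample size are untouched. This is a free improvement, not a flaw that threatens the trial.

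**What to change.** In the Statistical analysis section, state that:

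1. The comparison with healthy participants uses baseline GAD data and is one planned independent-groups contrast, both randomised arms pooled versus healthy, reported as an estimate with a 95% CI.
2. For measures that are not normally distributed, it is a two-sample rank-sum test of pooled GAD versus healthy.
3. If three groups are ever compared on ranks, the test is Kruskal-Wallis, named as such.

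The word for pairing should be removed from the two-group rule, so that it fits independent groups. The number of patients giving stool should be stated, so that the precision of the microbiota comparison can be judged.

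The cost is a few sentences of analysis wording. The three analysis changes need no new data, visits or patients.
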